##### ***Control group***

Due to budget constraints, we are not able to provide a matched placebo as prespecified for the main study. Therefore, we will not give placebo for children in the control group, either in the mild or severe group. Children in the control group of the mild AOM group will still receive expectant observation and those in the severe AOM group will receive antibiotics, and other concomitant treatment based on physicians' preferences (if necessary). The only difference between the intervention and control group is solely whether they receive prednisolone (intervention group) or not (control group).

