### **2.2.3.3 Adherence monitoring**

Participating physicians will provide information regarding the administration of the prednisolone. The researcher will send a daily text-message reminder to all the parents in both prednisolone and control groups during the intervention period of five days to take the drug regularly and to complete the symptom diary daily. The text-message will also remind all the parents to visit the clinic after the 48-hour expectant observation or visit-1 (day-3), visit-2 (day-7), visit-3 (day-30), and visit-4 (day-90) for re-assessment. At each visit-1 and visit-2, the parents will return the first and second mini-booklets of symptom diary and the left-over drug to the appointed nurse (at visit-2). The nurse will then check the symptom diaries and the left-over drug for the adherence in taking intervention drugs. We will visit the patients' homes to collect the third mini booklet of symptom diary that will record the symptoms from day-7 to day-14 after the baseline visit.

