### ***The compliance to study and study drug***

The compliance to study and study drug is defined as a proportion of children who regularly take the study drug (assessed using the symptom diary and any left-over drug) and come to follow-up visits per protocol. Participants will be followed-up closely by clinicians and research staff. Children will return for a visit at day-3 after randomisation, ensuring collection of the primary outcome.

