### 2.1.6 Sample size

We did not determine a sample size for the pilot study. There are several suggestions in calculating the sample size for a pilot study (e.g. at least 55 participants or at least 9% of the sample size of the main study) [39]. Since we will need 60 children in the mechanistic sub-study, we will include 60 children with AOM in our pilot study. The sample size of the mechanistic study was determined based on the main primary outcome, which is the mean value of static acoustic admittance or acoustic compliance in the tympanogram. In a previous study of children with middle ear effusion (MEE) who underwent tympanometry assessment and had a history of chronic or recurrent middle ear disease [40], the response within each subject group was normally distributed with standard deviation 0.3. If the true difference in the experimental and control means is 0.3 units, we will need to study 22 experimental subjects and 22 control subjects to be able to reject the null hypothesis that the population means of the experimental and control groups are equal with probability (power) 0.9. The Type I error probability associated with this test of this null hypothesis is 0.05. With a 20% allowance for dropouts, the total sample size becomes 56 or we will include 60 children for this pilot study.

Using the worst-scenario that of 50 physicians who work at seven appointed hospitals and have approximately 97 patients with AOM per week, we estimate that only 30% of the physicians will confirm their participation and 25% of the patients will give their consents to participate in our study. We then estimate that it will require nine months to recruit 60 children with AOM in this pilot study, including the extra months for potential slow recruitment and last follow-up (three months after the baseline visit).

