## **2.4 Data collection, management, and analysis**

### **2.4.1 Data collection methods**

We will assess the outcomes using CRFs, patient symptom diary, and feedback forms. The CRFs consist of eligibility-and-randomisation, baseline history, outcomes, serious adverse events (if applicable), and drug dispensing and returned forms. The outcome form will record the severity of pain and overall symptoms with their durations using VAS and AOM-SOS, as well as the resolution of AOM signs using otoscopic and tympanometry examinations (for the mechanistic study).

We will identify the recruitment rate by assessing the proportion of children who provide their consents divided by the proportion of consultations with potentially eligible children during the trial. We will use the informed consent and a study recruitment log book to record the reason(s) why children were not randomised.

We will assess the success of the study procedures using feedback forms. On the feedback form, patients and their parents and participating physicians will rate their understanding and challenges

they have during the implementation of study procedures (e.g. obtaining the randomised 2-digit patient ID numbers and their allocation of the treatment, completing the informed consent forms and CRFs) using grading scale ranged from one to five (1=very easy; 2= easy; 3=moderate/neutral; 4=difficult; 5=very difficult).

To assess the ability to measure planned outcomes in main study, we will also use a feedback form to identify the understanding, the challenges, the complexity of the outcome assessment tools utilised for this study (e.g. CRFs and patient symptom diary which includes VAS and AOM-SOS) from the perspective of the patients and their parents and the participating physicians. The CRFs and symptom diary will record the clinical history and symptoms (e.g. VAS, AOM-SOS), as well as physical examination (e.g. temperature, blood pressure, otoscopic examination if feasible). This information will be obtained from the perspectives of the patients and their parents and the clinicians.

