#### **2.4.3 Statistical methods**

For the recruitment rate, we report the outcome as the proportion of children in percentages (%). For the success of the study procedures and the ability to measure planned outcomes in main study, we will report the outcomes as the proportion of clinicians in percentages based on the grading

scale of their feedback reporting on prespecified outcome measure tools. For the compliance to study and study drug, we will report the outcomes as the proportion of children in percentages who attend the follow-up visits and complete the cycle of study drug.

To assess the verification of sample size calculation for main study, we will report this outcome as the proportion of children in each stratum (mild and severe AOM group) and those with pain at Day-3 after randomisation in the control group.

For the mechanistic sub-study, we will report continuous variables (i.e. the change in MEE at various time points (mean in days standard deviation), the duration of MEE) as a mean difference (MD) with 95% confidence intervals (CI) also the difference between two groups. We also will report the correlation between ear pain and other symptoms with the changes in MEE at various time points.

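### Measurability and procedure success are reported from clinicians' ratings alone, with no count of children who have a usable day-3 VAS, and compliance merges drug-taking and attendance without naming an arm

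*Protocol*

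**What the plan says.** **Procedures and measurability.** Protocol section 2.4.3 (Statistical methods) covers two pilot outcomes in one sentence, the success of the study procedures and the ability to measure the main study's planned outcomes: "we will report the outcomes as the proportion of clinicians in percentages based on the grading" scale of their feedback. Section 2.4.1 (Data collection methods) has a wider set of raters. On the feedback form, "patients and their parents and participating physicians will rate their understanding and challenges" on a scale from one to five, and views on the outcome tools are sought from the same groups. Section 2.2.4.1 takes the main study's day-3 pain outcome from a VAS in the patient symptom diary. Under Recruitment of participants (section 2.1.7), parents complete that diary with the physician's help.

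**Compliance.** Section 2.2.4.1 defines it as "a proportion of children who regularly take the study drug" and come to follow-up visits. Section 2.4.3 reports "the proportion of children in percentages who attend the follow-up visits and complete the cycle of study drug". Neither names an arm. Section 2.2.3.1 says of the controls: "we will not give placebo for children in the control group".

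**Reminders.** Section 2.2.3.3 plans a daily "text-message reminder to all the parents in both prednisolone and control groups during the intervention period of five days to take the drug", and section 2.2.5 repeats this for all parents.

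**Recruitment.** Sections 2.2.4.1 and 2.4.3 give a simple proportion. Section 2.4.1 describes instead "the proportion of children who provide their consents divided by the proportion of consultations with potentially eligible children during the trial".

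**The concern.** The pilot's first objective (section 1.2) is to test the main study's procedures and outcome tools. The tool that matters most is the diary VAS at day 3, and the people who must use it daily are the families. Section 2.4.1 itself expects some low-literacy parents to need help with the diary for two weeks. A summary of clinicians' ease ratings does not show whether families coped, and no ease rating shows whether the data arrived. The pilot could therefore describe measurement as easy without stating how many children had the data for the main study's primary outcome.

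The compliance figure has a related weakness. About half the children have no drug to complete, and a child can fail the joint criterion through the drug or through attendance. One pooled percentage does not separate these, and they call for different remedies in the main study.

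**Working it through.** **1. Sample size and split.** Inputs from section 2.1.6: SD 0.3, difference 0.3, power 0.9, type I error 0.05 (taken as two-sided), 20% dropout.

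- n per arm = 2 × (1.960 + 1.282)² × (0.3/0.3)² = 21.01, which rounds up to 22. This agrees with the protocol (t-test power at 22 per arm is 0.8997).
- 22 / (1 − 0.20) = 27.5, so 28 per arm and 56 in total, also as stated. The protocol then settles on "we will include 60 children with AOM in our pilot study".
- With 1:1 allocation (section 2.1), about 30 children receive prednisolone and about 30 are controls.

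**2. Who rates, and who is reported.**

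| Item | Section 2.4.1 collects | Section 2.4.3 reports |
|---|---|---|
| Ease of procedures | patients/parents and physicians | clinicians |
| Ease of outcome tools | patients/parents and physicians | clinicians |
| Completion of diary and CRFs (under compliance) | yes | not mentioned; only attendance and drug completion |
| Proportion of children with a usable day-3 VAS | can be derived from diary and CRFs | not a stated measure |

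Number of raters: section 2.1.6 takes a worst case in which 30% of 50 physicians take part, so 0.30 × 50 = 15, against up to 60 families.

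- Half-width of a 95% interval at p = 0.5, from 1.96 × √(0.25/n): 0.253 for n = 15 and 0.127 for n = 60.
- Wilson 95% interval at an illustrative 80%: 12/15 gives 55% to 93%; 48/60 gives 68% to 88%.

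**3. Compliance.** If the joint criterion is applied to all 60 children, the maximum is 30/60 = 50%.

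| Compliant children in the prednisolone arm | Over all 60 | Over the 30 on prednisolone |
|---|---|---|
| 21 | 35% | 70% |
| 24 | 40% | 80% |
| 27 | 45% | 90% |
| 30 | 50% | 100% |

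**4. Recruitment wording.** Let T be consultations, E potentially eligible children and C consenting children. The definition in section 2.2.4.1 is C/E. The phrase in section 2.4.1 can be read in two ways:

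- (C/T) / (E/T) = C/E, the same rate.
- (C/E) / (E/T), a different quantity.

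With illustrative counts T = 1000, E = 240 and C = 60 (25% consent, as assumed in section 2.1.6), the first reading gives 25% and the second gives 0.25/0.24 = 104%.

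**The case against.** **Clinicians are not the wrong people to ask.** They help parents with the diary and complete the outcome form, which also records VAS and AOM-SOS. This is right: they are an incomplete group of raters, not an irrelevant one. It does not explain why ratings collected from families have no place in the report.

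**Missing day-3 data would probably surface.** Section 2.2.4.1 promises a narrative report of the clinical outcomes, section 2.4.1 counts diary and CRF completion under compliance, section 2.4.2 logs missing data, and section 2.4.3 reports day-3 pain in controls. This softens the risk. Even so, none of these makes the proportion of children with a usable day-3 VAS a stated result, and the last covers only one arm.

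**The compliance denominator is not fixed on all children.** A reader might infer that compliance is certain to be capped at 50%. The protocol does not say so. Drug adherence is checked from left-over drug, which controls do not have, and section 2.4.1 lists attendance and drug completion as separate items. Against this, section 2.4.3 names an arm where it wants one (day-3 pain in the control group) and names none here. The cap is therefore conditional. Denominator detail is often left to an analysis plan, but a definition that mixes two measures, one of which controls cannot meet, is a fault in the protocol text.

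**Three further inferences are not supported.**

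- Recruitment is not planned as a ratio of two proportions. The odd wording is confined to section 2.4.1, and under one reading it gives the right rate.
- The reminder text does not show that controls will take the drug. Under section 2.3.1 the nurse releases the prescription only to children allocated to prednisolone.
- These are not the pilot's primary outcomes. The protocol labels none of the pilot outcomes primary and uses that term only for the tympanometry sub-study.

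**Conclusion.** The point holds in limited form.

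- **Firm.** Section 2.4.3 reports two pilot outcomes from clinicians only, in conflict with section 2.4.1, and no stated measure gives the proportion of children with a usable day-3 VAS. The size depends on participation: about 15 raters in the protocol's worst case, with up to 60 families' ratings unreported. The main loss is of the users' perspective and of a completeness count; precision is secondary.
- **Conditional.** Compliance merges two measures with no arm named. If all 60 children form the denominator and the split is 30/30, the figure cannot exceed 50% and is half the prednisolone-arm rate. If only treated children are meant, the cap disappears, but drug and attendance failures stay merged and control-arm attendance goes unreported.
- **Minor.** The reminder sent to both arms contradicts the description of the control group, and the recruitment wording in section 2.4.1 differs from the definition in section 2.2.4.1. Both need reconciling. Neither shows a wrong planned computation or actual contamination.

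The sponsor should make these changes. The sample size is unaffected.

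**What to change.** In section 2.4.3:

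1. **Ability to measure outcomes.** Report the proportion of randomised children with an evaluable day-3 VAS, and likewise AOM-SOS, each with a 95% CI. Say what evaluable means. Because the planned outcome is a reduction in pain, the VAS needs both a baseline and a day-3 reading.
2. **Feedback ratings.** Report patients' and parents' ratings and clinicians' ratings separately, for procedures and for outcome tools.
3. **Compliance.** Report drug completion among children allocated to prednisolone, and visit attendance separately for each arm. Align the definition in section 2.2.4.1.

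Elsewhere, reconcile the reminder text in sections 2.2.3.3 and 2.2.5 with the control group described in section 2.2.3.1. Align the recruitment wording in section 2.4.1 with section 2.2.4.1, as consenting children over potentially eligible children in the log.

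The cost is a change of wording and a little more tabulation. The diary, CRFs, feedback forms, left-over drug counts, attendance records and recruitment log are already planned. The main drawback is that a completeness figure and families' ratings may look less favourable than clinicians' ratings alone.

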## CHAPTER 2 – METHODS

### 2.1 Trial design

This study is a pilot of a parallel, pragmatic, stratified, randomised, open-label, single-blind controlled trial of corticosteroids, as monotherapy for mild AOM, and in addition to individually prescribed antibiotics for severe AOM. In the main study, we will stratify eligible children based on the clinical specialty (primary care or secondary/tertiary care) and severity of AOM (mild or severe). However, for this pilot study, we only include ear-nose-throat-specialists (ENTs) who work at tertiary centres for the convenience of the implementation of the mechanistic sub-study as tympanometry is only available at the hospitals (tertiary centres). Therefore, we will stratify the children based on their AOM severity and then will randomly allocate to corticosteroid (prednisolone) or control (usual care without prednisolone) (Figure 1) with the allocation ratio of 1:1. Because it is an open-label study, the parents/caregivers and an appointed nurse who will perform the randomisation will be aware of treatment allocation, whilst the clinicians and tympanometry technicians will remain unaware of the treatment.

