### ***Ability to measure planned outcomes in the main study***

We will assess the ability to measure planned outcomes in main study, which are: (1) the proportion of children with pain reduced by at least the minimum clinically important amount, at day-3 after randomisation. This will be assessed using a VAS recorded in the patient symptom diary; (2) the severity of pain and other AOM-relevant symptoms at various time points using VAS, AOM-SOS, and the symptom diary; (3) duration to AOM resolution; (4) adverse effects, defined using standard clinical trials criteria, recorded in the diary, and reported to the central office and ethics committee as required.; (5) complications of AOM (e.g. perforation of tympanic membrane(s), mastoiditis); and (6) AOM recurrence, defined as a new episode of AOM at one to three months after randomisation. We will report these narratively due to a limited sample size and insufficient formal power calculation for this pilot study to be able to detect actual effects of corticosteroids to improve clinical outcomes in AOM.

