## **2.2.4.2. The mechanistic or tympanometry sub-study outcomes**

### **Primary outcomes**

#### ***The change in middle ear effusion (MEE) at various time points***

We will assess the change in the MEE at the following time points: baseline visit, visit-1 (day-3), visit-2 (day-7), visit-3 (day-30), and visit-4 (day-90). We will measure MEE using static acoustic admittance, defined as “the amount of energy absorbed by the tympanic membrane and middle ear, measured in mmho or mL” [38]. We will also measure the difference of this results between the intervention and control group.

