### The correlation between ear pain and other symptoms with the changes in MEE at various time points

We will identify the correlation between ear pain and other symptoms (i.e. ear tugging, irritability, crying, lack of sleep, lack of appetite, less of playfulness, fever) with the changes in MEE at various time points.

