### **2.3.2 Blinding (masking)**

In this study, the appointed nurses and the children and their parents will know the allocation of the intervention. We will ensure that the participating physicians and the audiologists/tympanometry technicians will be blinded to the intervention allocation during the study.

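### The symptom–effusion correlations in the mechanistic sub-study carry no term for arm or severity stratum, so a coefficient taken across arms would partly reflect allocation

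*Protocol*

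**What the plan says.** Section 2.2.4.2 lists the correlation as a secondary outcome of the sub-study: "We will identify the correlation between ear pain and other symptoms", followed by seven named symptoms, against change in MEE at several visits. Section 2.4.3 repeats it: "We also will report the correlation between ear pain and other symptoms with the changes in MEE at various time points". Neither place names the coefficient, treatment arm or severity stratum. The sentence before it in 2.4.3, on mean differences, does mention the comparison between groups.

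The two variables have different sources.

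- **Effusion.** Section 2.2.4.2: "We will measure MEE using static acoustic admittance". Section 2.1 says that "the clinicians and tympanometry technicians will remain unaware of the treatment".
- **Pain.** Section 2.2.4.1, on pain at Day 3: "This will be assessed using a VAS recorded in the patient symptom diary". Under 2.3.2, "the appointed nurses and the children and their parents will know the allocation of the intervention", and 2.2.3.1 states that controls receive no placebo.

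Randomisation is stratified by severity (2.1). Only the severe stratum starts on antibiotics; the mild stratum is observed for 48 hours (2.2.3).

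**The concern.** A correlation computed over all children combines two things: the association among children treated alike, and the covariance created when the arm means of both variables differ. The second part is present even if symptom and effusion are unrelated within each arm.

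Both conditions are plausible here. The sub-study is planned around an arm difference in admittance. Reported pain could differ by arm because the reporters know the allocation, or because prednisolone acts on pain or fever directly. Severity can work the same way: 2.2.4.1 defines the severe stratum partly by symptoms and partly by ear findings, and antibiotic use at baseline differs between strata.

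At stake is the meaning of the only planned analysis that relates effusion to symptoms. An unadjusted coefficient could be taken to show that children feel better because the effusion clears, when it reflects two parallel consequences of being given prednisolone.

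**Working it through.** **Inputs from the Protocol.** Arm difference in admittance 0.3 and SD 0.3 (2.1.6); 1:1 allocation (2.1); 22 per arm, 20% dropout, 56 and then 60 children (2.1.6); 35% severe (2.2.4.1, a planning figure for the main study). **Assumed, not in the Protocol:** the arm shift in reported pain, and the differences between strata in both variables.

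**Step 1: the plan's own figure.** Section 2.1.6 reads "If the true difference in the experimental and control means is 0.3 units". The standardised effect is 0.3 / 0.3 = 1.0. Then n per arm = 2 × (1.960 + 1.282)² / 1.0² = 21.0, rounded up to 22. For dropout, 22 / 0.8 = 27.5, so 28 per arm and 56 in total. The stated 22 and 56 reproduce, so the plan does rest on a 1-SD arm effect.

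**Step 2: correlation induced by arm alone.** Let d1 be the arm effect on MEE and d2 the arm shift in reported pain, both in within-arm SDs, with zero correlation within arms and half the children in each arm:

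|r| = (d1·d2/4) / √[(1 + d1²/4)(1 + d2²/4)]

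With d1 = 1.0:

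| d2 (assumed) | Calculation | \|r\| |
|---|---|---|
| 0 | 0 | 0 |
| 0.3 | 0.075 / √(1.25 × 1.0225) | 0.066 |
| 0.5 | 0.125 / √(1.25 × 1.0625) | 0.108 |
| 1.0 | 0.250 / √(1.25 × 1.25) | 0.200 |

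The sign depends on direction; higher admittance with lower pain would give a negative coefficient. If the arm effect on MEE is only half the planned size (d1 = 0.5), the values at d2 = 0.5 and 1.0 fall to 0.059 and 0.108.

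**Step 3: effect of adjustment.** In simulation (20,000 trials per setting, N = 44 and 60, no association within arms), the arm-adjusted correlation averaged 0.00 in every setting, to within 0.004. The unadjusted one matched the formula, for example 0.107 and 0.109 at d2 = 0.5 with d1 = 1.0.

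**Step 4: severity.** With 35% severe, replace 1/4 by 0.35 × 0.65 = 0.2275. Assumed differences between strata of 0.5 SD in both variables give 0.0569 / 1.0569 = 0.054, and 1.0 SD in both gives 0.2275 / 1.2275 = 0.185. Combining arm (1.0 and 0.5) with severity (0.5 and 0.5): (0.125 + 0.0569) / √(1.3069 × 1.1194) = 0.15.

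**Step 5: price of adjustment.** On Fisher's z scale the standard error rises from 1/√(N − 3) to 1/√(N − 5) with two adjustment terms. The ratio is √(41/39) = 1.025 at N = 44 and √(57/55) = 1.018 at N = 60, so the interval is about 2% wider.

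**The case against.** The strongest reply is that the Protocol is silent rather than wrong. It neither says that arms are pooled nor rules out adjusted or arm-specific estimates, and such detail is often left to a statistical analysis plan, which is not at hand. That largely stands: the point is a worthwhile improvement, not an error in the text. It survives because the Protocol does specify an analysis, a plain correlation, which if carried out as written has the weakness shown above.

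Four stronger readings are tempting, and the Protocol does not support them.

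- **A single trial-wide coefficient is planned.** Ear pain and seven other symptoms at several visits imply many correlations.
- **The plan will produce false-positive findings.** In the simulation, a 5% test of the unadjusted coefficient with d1 = 1.0 and d2 = 0.5 rejected in 10.6% (N = 44) and 12.9% (N = 60) of trials. But the Protocol plans no test of these correlations; it only reports them. The induced values up to 0.20 also lie below the 5% critical |r| of 0.297 (N = 44) and 0.254 (N = 60).
- **The sub-study exists to link effusion with symptoms.** Section 1.2 gives its aim as the effect of corticosteroids on resolution of effusion. The primary outcome addresses that by arm, using assessors intended to be blinded.
- **Adjustment reveals a link within children.** It gives an association between children treated alike. A within-child link would need a repeated-measures analysis.

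It is also fair that the 1-SD effect is a planning value for mean admittance, not a forecast for change at every visit, and that the shift in pain has no source in the documents.

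**Conclusion.** The point holds as a low-cost improvement. A symptom–MEE correlation taken across arms would partly reflect allocation, because the symptom reporters are unblinded and the sub-study is planned around an arm effect on MEE. Under the plan's own 1-SD effect and no association within arms, the induced |r| is about 0.07 to 0.20 for assumed pain shifts of 0.3 to 1.0 SD. It is zero if either arm effect is absent and smaller if the MEE effect is below plan. Severity could add to it, to about 0.15 in the combined example, again on assumed shifts. These are small to moderate distortions. They bear only on how one secondary outcome of a pilot is interpreted; the primary MEE comparison between arms is unaffected.

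**What to change.** Add to section 2.4.3 that each symptom–MEE correlation, at each visit where both are measured, is estimated adjusted for randomised arm and severity stratum (pooled within group) and reported with a 95% confidence interval. Add that any unadjusted coefficient is descriptive only and is not evidence that change in effusion explains symptoms.

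Two additions are optional. A rank-based coefficient would suit the three-level AOM-SOS items, though the VAS is a 100-mm scale. Arm-specific coefficients could be shown alongside, but with 22 completers per arm they would be imprecise. If the investigators want a within-child link, they should specify a repeated-measures analysis instead.

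The cost is a sentence or two, no new data, and about two degrees of freedom per correlation. Both adjustment variables are already recorded at randomisation.
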